#### Visual Stimuli Selection

We aim to identify the perceived familiarity of a range of food items among a test sample to categorize them into “highly familiar,” “familiar,” “somewhat familiar,” or “novel” for the main study. This will ensure that the familiar or novel food stimuli in the main experiment reflect participants’ everyday experiences. In this regard, we will create a list of food items, including a diverse range of food items from the categories we plan to use in the main study (eg, milk, oil, sauces, and beverages). Food products of “everyday” life, which have moderate visual complexity (no complex dishes), will be chosen as possible stimuli. To achieve a balanced set, we will include items commonly found in the target population’s diet (eg, whole milk, olive oil) and novel items they are less likely to encounter (eg, hemp milk, truffle oil). We will organize the food items into the categories we will be using in the main study to facilitate easy comparison (eg, “Beverages” might include orange juice, kombucha, and matcha latte). Accordingly, we will create a structured survey using Google Forms where each item will be rated based on familiarity using a Likert scale: 1=highly unfamiliar (I have never seen or heard of this product); 2=somewhat unfamiliar (I have rarely seen or heard of this product); 3=somewhat familiar (I know of this product but don’t use it often); 4=familiar (I use this product occasionally); and 5=highly familiar (I use this product regularly). We aim to recruit 100 participants to ensure diverse responses, taking demographic diversity (eg, age, gender, dietary preferences) into account to get a representative sample. Before launching the main survey, we will conduct a small pilot test with a handful of individuals (5-10 people) to identify any issues with wording, scale clarity, or question order.

Finally, we will calculate the mean familiarity score for each food item and classify items based on their mean familiarity score, based on the following scores:

Highly familiar: average score of 4-5Familiar: average score of 3-4Somewhat familiar: average score of 2-3Unfamiliar: average score of 1-2

Items falling into the “Highly Familiar” or “Familiar” categories will be used as familiar stimuli, while those in the “Unfamiliar” category can serve as novel stimuli for the main study. Based on the survey results, we will select the top 2 items from each category (eg, milk, oil, sauces, biscuits, and beverages) to be used as stimuli in the main study. Special care will be taken to select pictures of good quality, comparable lighting, and size. The pictures of each pair will be shown side by side and matched as closely as possible with regard to the shape, color, and position of the photographed object as well as background color. One choice out of the 5 choice sets (milk, oil, sauces, biscuits, and beverages) will be used as a warm-up to familiarize the participants with the procedure and will not be included in the data analysis.

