While some previous studies have suggested a role for visual attentional bias toward familiarity and novelty of stimuli [22], there is a paucity of studies using electroencephalography to examine this, particularly in the context of food choice behavior. Electroencephalography is a noninvasive technique used to measure brain activity in response to stimuli by recording event-related potentials (ERPs). So far, only a few studies have explored integrating electroencephalography, eye-tracking, and dot-probe methods to study attentional bias to food-related stimuli [23]. Of note, no previous study has taken stimulus novelty and familiarity into consideration, nor how the results of this integrated approach associate with the self-report food choices. Familiar stimuli evoke trust and perceived quality from previous positive experiences are suggested to influence an individual’s choices [24]. However, novel products require more cognitive effort to evaluate, leading to longer information processing times [25]. Thus, the main objective of this pilot study is to examine differences in attention to novel compared with familiar food stimuli, using 3 different attention indexes, including electroencephalography, eye tracking, and dot-probe. Indeed, it is hypothesized that participants will exhibit shorter reaction times (RTs) and longer total fixation durations (TFDs) for familiar compared to novel food items, indicating a stronger attentional bias toward familiar foods. In addition, familiar food items will elicit greater P300 amplitudes compared with novel food items, suggesting enhanced attentional engagement and processing.

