#### Eye Tracking

The eye-tracking component of this study will be conducted using the Tobii Nano Pro (Tobii Tech), a screen-based eye tracker known for its high precision in capturing gaze data. The Tobii Nano Pro offers a sampling rate of 60 hertz, which translates to data collection at intervals of 16.67 milliseconds. This high frequency allows for detailed tracking of eye movements and gaze patterns. To ensure accurate gaze data, a standard 9-point calibration procedure will be performed at the beginning of each session. This process involves directing the participant’s gaze to 9 specific points on the screen to map their eye movements accurately. The calibration will be verified for precision before starting the main trials to ensure reliable spatial and temporal tracking. Participants will be seated approximately 60 cm from the Tobii monitor, which has a resolution of 1600 × 1200 pixels. Participants will be instructed to maintain a still head position and focus attentively on the images displayed on the screen. Participants will view pairs of pictures displayed side by side for 500 or 2000 milliseconds each. Each image pair is matched for shape, color, and background to control for these variables. The following eye-tracking parameters will be measured:

TTFF: time elapsed between the appearance of a picture and the user’s initial gaze fixation within an area of interest. In this case, each product will be defined as a separate area of interest.First fixation duration: time participants gaze at their first fixation point.TFD: length of all fixations within a specific area of interest (in seconds). Average TFD will be used for statistical analyses.Fixation count: number of fixations on stimuli.Eye movement data will be analyzed using Tobi software.

Fixations are defined as periods where the gaze remains stable within a 30-pixel radius for at least 100 milliseconds, and these fixations must be initiated at least 100 milliseconds after picture onset to exclude anticipatory eye movements.

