While previous research has explored the effects of familiarity on consumer preferences and decision-making [35,36], the combined use of eye-tracking and electroencephalography metrics remains underexplored, particularly when taking the participant’s food choice into consideration. The integration of these technologies allows for a comprehensive analysis of both spatial and temporal aspects of attention, capturing where and how long participants focus on food stimuli and the neural dynamics underlying these attentional processes [37]. Previous research has highlighted the relevance of visual attention in the food decision-making process. For instance, in the study by Gere et al [38], the authors proposed using alternative models to analyze visual attention patterns during food choices. Their approach emphasized the use of multimodal data, such as eye-tracking and neurophysiological measures, to predict food preferences and decision outcomes more accurately, which supports the use of combined methodologies in our pilot study to capture these intricate cognitive processes. In addition, Wang et al [39] used eye-tracking and electroencephalography to investigate how emotional states influence attention to food-related stimuli. The findings revealed distinct neural patterns associated with processing positive versus negative stimuli and suggested that emotional context significantly modulates visual attention towards food. This insight aligns with our aim to explore potential neural mechanisms (eg, P300 and N100 ERP components) that may underlie attentional biases in response to food stimuli, indicating that factors such as familiarity and novelty could similarly impact cognitive responses. Furthermore, research comparing attentional differences in overweight or obese versus normal-weight females under hunger and satiety conditions demonstrated that hunger states amplify attention to high-calorie foods, while satiety reduces such biases [23]. These findings suggest that attentional biases are dynamic and can be influenced by both physiological states and personal food-related experiences.

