Integrating these perspectives, our study seeks to build upon these observations by investigating how familiarity and novelty interact with attentional biases, potentially offering a new understanding of how these factors shape food choices. A recent study investigating electroencephalography measures of attention toward food-related stimuli in neophobic individuals proposed that food neophobia might be associated with attentional biases toward novel foods. However, the results indicated that implicit behavioral and attentional processing were affected across all food types, regardless of familiarity [40]. This finding, alongside several other studies [23,41] examining attentional differences toward food stimuli based on factors such as calorie content and familiarity across diverse populations, underscores the importance of using multiple methods to capture different dimensions of attention. This study serves as an initial step in piloting an integrated approach, combining electroencephalography, eye tracking, and a dot-probe task, to gather preliminary data on the feasibility of using this multimodal framework to assess attentional responses to familiar versus unfamiliar food stimuli in healthy adults. A recent systematic review and meta-analysis on attentional bias toward food in individuals with overweight and obesity [42] highlighted the poor reliability of eye tracking and the dot-probe task, 2 commonly used methods for measuring attentional bias. The review emphasized that the poor psychometric properties of these measures represent a significant limitation in attentional bias research. In light of this, the present study’s integration of 3 different attentional bias tools is a key strength, offering a more comprehensive approach to capturing multiple dimensions of attentional processes. In addition, this study has several other strengths. First, the integration of eye-tracking, electroencephalography, and the dot-probe task is a novel approach that allows for a comprehensive analysis of attentional biases towards food stimuli. Second, by examining attentional biases toward familiar or novel food stimuli, the study addresses an important aspect of consumer behavior with implications for both health behaviors and marketing strategies. Third, the use of multiple measures (eg, TTFF, TFD, RTs, P300, N100) enhances the reliability of the findings and provides a solid foundation for validating results in future studies.

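### Energy content is controlled neither in pairing the foods nor in the attention ANOVA, so with few shared products a product difference could be read as a familiarity effect

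*Protocol article*

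**What the plan says.** The main objective is to "examine differences in attention to novel compared with familiar food stimuli" (Introduction). The Introduction and Principal Findings say that shorter reaction times, longer fixation and larger P300 for familiar items will be taken as bias towards, or greater engagement with, familiar foods.

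Visual Stimuli Selection describes how the foods are chosen:

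- In a survey, "each item will be rated based on familiarity using a Likert scale". No other rating of the items is described.
- Candidates are grouped by category. They include common products such as whole milk and olive oil, and "novel items they are less likely to encounter (eg, hemp milk, truffle oil").
- On the pictures: "Special care will be taken to select pictures of good quality, comparable lighting, and size". The two pictures of a pair are "matched as closely as possible with regard to the shape, color, and position of the photographed object as well as background color".

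The Eye Tracking section repeats the matching: "Each image pair is matched for shape, color, and background to control for these variables".

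Statistical Analysis specifies a repeated measures ANOVA with stimulus type across four food categories as the within-subject factor and presentation time as the between-subject factor. It names no food property and no item-level term.

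The Discussion (Principal Findings) cites evidence that "hunger states amplify attention to high-calorie foods", and refers to studies "examining attentional differences toward food stimuli based on factors such as calorie content and familiarity across diverse populations". The limitations paragraph says that satiety status is not included. It mentions the small number of food categories only as a limit on the range of foods covered.

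**The concern.** Familiar versus novel is a within-participant contrast, so each person is their own control and differences between people largely drop out. Differences between the products do not. The two foods in a pair are different products, and anything about them that draws the eye apart from familiarity is part of the contrast. Picture matching removes low-level visual differences, and pairing within a category removes gross differences in food type. Energy content is left free, although the protocol's own Discussion names it beside familiarity as a factor in attention to food.

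The ANOVA judges the familiar/novel difference against variation between participants. Because all participants see the same products, a product-specific difference shifts everyone's mean together and does not enter that error term. More participants or repetitions make the shift easier to detect and do nothing to reduce it.

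At stake is the wording of the main conclusion. A significant difference would be reported as bias towards familiar foods, with no planned check on whether a few particular products produced it. The shift may also run against a true familiarity effect and hide it.

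**Working it through.** **The plan's own figure.** Sample Size gives f = 0.35, α = 0.05, 2 groups, 8 measurements, correlation 0.5, N = 40 and power 0.820. The between-groups formula gives λ = f²·N·m / (1 + (m−1)ρ) = 0.1225 × 40 × 8 / 4.5 = 8.71 on 1 and 38 df, and power 0.8202. The figure reproduces, but for the presentation-time effect. It does not bear on the familiar/novel contrast or on product differences.

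**How many pairs?** The Dot-Probe Task section gives 128 trials and 8 displays per image pair.

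- One pair in each of 4 categories would give 4 × 8 = 32 trials, or 64 if shown at both durations. Neither is 128.
- 128 / 8 = 16 pairs, which fits 2 familiar × 2 novel items crossed in each of 4 categories.
- 8 pairs shown 8 times at each of two durations also gives 8 × 8 × 2 = 128.

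The trial count therefore points to 8 or 16 pairs. Choosing the top 2 items per category (Visual Stimuli Selection) leaves 4 conceivable, so all three are shown.

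**False-positive rate.** Suppose there is no true familiarity effect. Pair j carries a product difference drawn from N(0, s²), the same for all participants, and the contrast averages J pairs. The unit for s is the between-participant SD of the mean familiar-minus-novel difference. The t statistic is then distributed as k·t with 38 df, where k = √(1 + N·s²/J), and

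rejection rate = 2·P(t₃₈ > 2.024 / k).

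Example with N = 40, J = 4, s = 0.2: N·s²/J = 0.4, k = 1.183, 2.024 / 1.183 = 1.711, rate 9.5%.

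| Pairs (J) | s = 0.2 | s = 0.3 | s = 0.5 |
|---|---|---|---|
| 4 | 9.5% | 15.0% | 28.6% |
| 8 | 7.2% | 10.1% | 18.5% |
| 16 | 6.1% | 7.5% | 12.1% |

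At s = 0.1 with 4 pairs the rate is 6.1%. The values of s are assumptions, since the documents give none. The row for 16 treats the pairs as independent. If they are 2 × 2 crossings of the same products, the mean is that of 8 familiar minus 8 novel products, with variance s²/8, and the row for 8 applies.

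**A shift on the same side in every pair.** A common shift of b SD gives a noncentral t with noncentrality b·√40. For b = 0.2 this is 1.265 and the rejection rate is 23%; for b = 0.3 it is 1.897 and the rate is 46%. More pairs do not change these figures.

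**Would a same-direction rule be a fair test?** A true effect detected with 80% power at N = 40 has noncentrality of about 2.87. With 4 pairs and differences uncorrelated across pairs (an assumption), each pair's own noncentrality is half of that, 1.44. The chance that one pair shows the right sign is Φ(1.44) ≈ 0.925, and that all four do is 0.925⁴ ≈ 0.73. Requiring agreement in every pair would therefore reject about 27% of true effects of that size.

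**The case against.** **Pairs are not matched on appearance alone.** A reader might infer that nothing but the picture is controlled. That goes too far: items are grouped and selected within a category, so milk is set against milk and oil against oil. This stands as a real partial control. It narrows energy differences without equating them; the beverage examples run from orange juice to kombucha and matcha latte. These are candidate items, and the article shows no actual pair with an energy gap.

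**Liking.** A reader might also treat liking as a confounder to be matched. The documents do not support this. The Introduction presents trust and perceived quality from earlier positive experience as part of how familiarity acts on choice, so matching on liking would remove some of the effect under study. Novel items are by definition ones that respondents have rarely or never met, so a liking score for them would mean little.

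**The evidence on energy is indirect.** The cited hunger finding compares overweight or obese with normal-weight women, whereas this study enrols adults with healthy BMI, and it does not concern products of the same category. This weakens any claim about size. The plan's silence on a factor that it names itself remains.

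**Item-level data will exist.** The Food Choice Questionnaire is completed for each item. That is true, but it comes after the task, is not in the attention ANOVA, and none of its listed subscales measures energy content.

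**This is a pilot, and analysis detail may sit elsewhere.** Four categories in the ANOVA make the interaction available, and per-pair tables often belong in an analysis plan. However, the article itself fixes the matching variables, in two places, and the interpretation of the result.

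**Conclusion.** The concern holds in a limited form. Energy content is addressed neither when the pairs are chosen nor when the attention measures are analysed, the products are few and the same for everyone, and the planned test cannot separate a product difference from familiarity.

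On the 8 or 16 pairs that the trial count suggests, the false-positive rate for familiarity would be about 6% to 19% instead of 5% for assumed product SDs of 0.2 to 0.5. The higher range, 9.5% to 29%, needs only 4 pairs. The ranking of these figures follows from the design; their size rests on SDs that the documents do not supply.

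A reader might infer that energy favours one side throughout, with error rates of 23% or 46%. The arithmetic is correct for shifts of 0.2 and 0.3 SD, but nothing in the article shows that such a pattern occurs. It is a reason to tabulate the energy values, not a finding about these foods.

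**What to change.** The abstract and the Results section report 36 and 34 of 40 participants enrolled, and the abstract says that analysis has not begun. A new selection rule would probably come too late, but the following can still be prespecified:

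1. In Visual Stimuli Selection, add a table of the products used, pair by pair, with label energy per 100 g or 100 ml, and state the number of pairs.
2. In Statistical Analysis, prespecify three results for each attention measure: the familiar-minus-novel difference for each pair, the stimulus type × category interaction, and the main effect with each pair left out in turn.
3. State the reading in advance: if the main effect depends on one pair, or the energy difference lies on the same side in all pairs, the result is reported as a difference between these products and not attributed to familiarity alone.

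Do not require the same direction in every pair, and do not add matching on liking.

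The cost is a label look-up and a little extra analysis of data already being collected. The conclusion may come out narrower.

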#### Intervention

Participants who meet the inclusion criteria will be recruited to complete a dot-probe task while integrated electroencephalography and eye-tracking data are recorded. Each participant will conduct a series of attention-related tasks (an eye-tracking task, a visual probe task, and an ERP task), and, hereafter, a Food Choice Questionnaire (FCQ) to assess food choice. The intervention involves presenting participants with both familiar or novel food items from 4 categories (milk, oil, sauce, and beverages) simultaneously during the dot-probe task to assess attentional biases. In this task, pairs of images (one familiar and one novel food item) will be displayed on a computer screen, followed by a dot-probe appearing in the location of either the familiar or novel item. Participants will be instructed to respond as quickly and accurately as possible by pressing a key corresponding to the location of the dot-probe. Reaction times to the dot-probe will be recorded. Neural responses will be captured using electroencephalography to identify specific brain activity patterns associated with processing the food stimuli, offering insight into the cognitive and neural mechanisms underlying attention. Eye-tracking technology will also be used concurrently to monitor gaze patterns and fixation duration (FD) on each food item, enabling us to quantify the amount of visual attention allocated to familiar versus novel items. No intervention modifications are planned in this study, as they do not apply to the type of intervention used.

#### Procedure

On the day of the main study, participants will first complete a demographic questionnaire. After this, they will have a brief period to relax and prepare for the tasks ahead. The study will use 3 attention indexes, all featuring the same food item images: an eye-tracking paradigm (measuring gaze direction and duration), a visual dot-probe task (assessing reaction times), and the recording of electrophysiological brain activity (evaluating the amplitude of the P300 and N100 ERPs). Before starting the tasks, electrodes will be positioned and adjusted, using the Cz electrode as the reference point (located at the center of the electroencephalography cap). A potassium chloride solution will be applied to the electrodes’ sponges to lower impedance to below 5 kΩ. Participants will then be seated 60 cm away from the eye-tracking system, with the camera calibrated to optimally capture their eye movements, followed by a 9-point calibration procedure to ensure accurate eye-tracking data. After successful calibration, participants will be instructed to keep their heads still and focus on the images displayed on the screen. They will read the instructions and complete 5 practice trials to familiarize themselves with the task.

Briefly, participants will be instructed to respond as quickly and accurately as possible by pressing a key corresponding to the dot’s location during a dot-probe task, with ERPs being recorded via electroencephalography. Participants’ gaze position will also be tracked every 16 milliseconds (60 Hz) throughout the experiment. The entire experiment will take place in a controlled environment, minimizing electromagnetic interference and maintaining consistent lighting. Once the integrated methods are completed and all recordings have been captured, participants will be asked to fill out the food choice questionnaire.

